### Intervention

Cytisinicline is administered as 1.5 mg tablets to all patients for 25, 50, or 75 days depending on arm allocation. The drug is produced and marketed by Adamed Pharma SA [name] (Poland).

According to the data sheet for cytisinicline, the D-day will be set as the date from which the smoker intends to quit smoking. This date cannot be later than the fifth day after the start of treatment with cytisinicline. This D-day should be decided by the patient with his doctor before starting treatment.

### Criteria for Discontinuation of Treatment/Intervention

A patient will be withdrawn from the study when the investigator becomes aware that a participant is experiencing a serious or intolerable adverse event that prevents continuation of the drug study.

The patient may also be excluded from the study at the investigator’s request (eg, if the investigator believes that the participant’s health could be compromised by continued treatment with the study drug). Noncompliance is not grounds for discontinuing treatment.

If a patient becomes pregnant during the study treatment period, treatment with the study drug must be discontinued. However, the participant must remain in the study to continue with safety and other study assessments.

Discontinuation may also occur at the participant’s request if they do not wish to continue drug treatment.

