## Methods

### Trial Design

Phase IV randomized, open-label, controlled, parallel, multicenter clinical trial in patients who are candidates for smoking cessation to demonstrate the superiority of maintenance therapy with cytisinicline compared to the standard regimen.

The trial was designed according to the standardized guide for interventional trial protocols, SPIRIT (Standard Protocol Items: Recommendations for Interventional Trials statement [Multimedia Appendix 2]). A total of 402 patients from 10 smoking cessation units in Spain will be randomized. Recruitment will last for one year, with a follow-up of 52 weeks per patient recruited. Candidate patients who sign the informed consent form will be randomized to 3 possible arms in a ratio of 1:1:1.

Arm A: control group. Participants randomized to this group will be treated with cytisinicline as stated in the data sheet. They must remain smoke-free from day 5 of treatment.

Arm B: maintained therapy 1. Following the standard regimen, these patients will maintain treatment for an additional 25 days at a dose of 1.5 mg twice daily.

Arm C: maintained therapy 2. Following the standard regimen, these patients will maintain treatment for an additional 50 days at a dose of 1.5 mg twice daily (see Table 1).

At the end of the treatments, participants will continue in the follow-up phase, without treatment, until completing 52 weeks in the study (see Figure 1).

**Table 1 table1:** Dosage guidelines in each of the 3 treatment arms.

Days of treatment		Recommended dosage	Maximum daily dose	Recommendations	

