### Specific Outcomes Efficacy

Different outcomes will be used to measure the efficacy of cytisine in each arm of the clinical trial.

The sustained abstinence rate will be determined in each of the three treatment arms at 6 and 12 months, based on carbon monoxide co-oximetry results in ppm. The correlation between the sustained abstinence rate in each of the three arms studied at 6 and 12 months, based on co-oximetry results, and the self-reported abstinence at 6 and 12 months will be calculated.

Additionally, point abstinence will be analyzed every 7 days in each of the 3 arms studied, based on the results obtained in the CO tests.

The percentage increase in abstinence rates will be compared with the increase in the duration of cytisinicline use. The number needed to quit smoking for one patient in each treatment group will also be calculated.

Interval abstinence will also be determined in this clinical trial. The abstinence rate will be analyzed from Day 25 to Day 50 in all 3 study groups and from Day 25 to Day 75 in all 3 study arms. The abstinence rate will also be determined from Day 25 (usual arm), Day 50 (extended arm 1), and Day 75 (extended arm 2) up to 6 and 12 months.

Relapse rates will be analyzed in each treatment arm. The frequency and percentage of relapses will be determined in those who quit smoking from Day 25 (usual arm), Day 50 (extended arm 1), and Day 75 (extended arm 2) up to 6 and 12 months in all 3 arms.

Craving and withdrawal symptoms will be assessed during the clinical trial. The mean Minnesota Nicotine Withdrawal Scale (MNWS) score and the mean craving score will be calculated at the initial in-person visit in all 3 arms, and their change from this visit will be measured on days 25, 50, and 75 in all 3 study arms.

Predictors of continued abstinence at 6 and 12 months of treatment and of relapse (clinical, anthropometric, demographic, and smoking-related variables) will be determined in all study arms.

Quality of life in each group will be calculated using the EQ-5D-5L scale score at baseline, 50 days, 90 days, 6 months, and 1 year.

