### Pharmacovigilance

As this is a low-intervention study, the expected adverse events are those reflected in the drug label. The definition of adverse events, the classification of their severity, and the actions to be taken by the principal investigator and sponsor in the event of an adverse event are included in Multimedia Appendix 1. In all cases, the sponsor should promptly communicate to the investigators any important information that could adversely affect the safety of the participants or the conduct of the trial. The communication of such information should be concise and practical. The communication shall be in accordance with the criteria and procedure specified in the European Commission’s guidelines. The sponsor shall report to the Spanish Agency for Medicinal Products and Health Products all suspected serious and unexpected adverse reactions associated with the investigational medicinal products of which he/she has become aware. An adverse event is an undesirable experience that affects a patient during a clinical trial or study, whether or not it is considered to be related to the investigational product.

A serious adverse event is one that is life-threatening, causes persistent disability, or requires prolonged hospitalization of the patient. Apart from these, congenital anomalies and malignant neoplasms shall always be considered serious.

A nonserious adverse event is any adverse event that does not meet any of the above criteria.

An unexpected adverse event is an experience that is not described in the investigator’s manual (by nature, severity, or frequency occurred in the clinical trial).

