### Ethical Considerations

The trial will be conducted in accordance with the requirements documented in the latest version of the Declaration of Helsinki (Helsinki, 2024) and with the Standards of Good Clinical Practice. The trial is authorized for conduct by the Galician (Spain) Committee on Ethics in Medicines Research with code 2025/043 and by the Spanish Agency for Medicines and Medical Devices. It also has the agreement of the participating centers. This trial has been registered in the European Clinical Trials Register under EUDRACT code 2024-518936-36-00.

The researchers at each center will provide each participant with a patient information sheet, approved by the clinical research ethics committee, informing them about relevant study data and requesting access to their clinical and personal data recorded in their medical history and disclosed during visits. Permission is also requested for tests, examinations, and questionnaires, and the patient is informed that these actions are part of their daily clinical practice. In addition, the researcher will verbally inform the patient about the trial and answer their questions to ensure they understand the implications of their participation. The patient will be informed of their right to withdraw consent at any time and their right to have their data deleted. The patient will be informed of the possibility of being withdrawn from the study for safety reasons (an adverse event caused by the study medication) or for failure to comply with established procedures.

No patient may be included who has not given written informed consent to participate in the trial. Secondary analyses using existing data are included in the primary consent and do not require additional consent.

The research team and the sponsor of this study expressly undertake not to disclose the identity of the patients treated and to respect the confidentiality rules regarding the data and information to which they have access by participating in the trial.

In order to guarantee the confidentiality of the trial data, only the sponsor and members of the research team, the Research Ethics Committee for Medicinal Products, and the relevant health authorities will have access to them.

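### As written, an adverse event that prevents continuation takes the patient out of the study, not only off the drug; only pregnancy is expressly handled as drug stopped, patient retained

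*Protocol article*

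**What the plan says.** The section Criteria for Discontinuation of Treatment/Intervention covers four situations.

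- **Serious or intolerable adverse event.** "A patient will be withdrawn from the study when the investigator becomes aware that a participant is experiencing a serious or intolerable adverse event". The sentence continues with a qualifier: the event must be one that prevents continuation. The rule is mandatory.
- **Investigator's safety concern.** "The patient may also be excluded from the study at the" investigator's request; the example given is a belief that the participant's "health could be compromised by continued treatment with the study drug". The rule is discretionary.
- **Pregnancy.** The drug must be stopped. "However, the participant must remain in the study to continue with safety and other study assessments".
- **Participant's request.** Only stopping the drug is mentioned; follow-up is not addressed. The same section says that noncompliance is no reason to stop treatment.

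Ethical Considerations says that patients will be told of "the possibility of being withdrawn from the study for safety reasons (an adverse event caused by the study medication"), and adds failure to follow the established procedures as a second ground for withdrawal.

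Two other places bear on the point. Trial Design says that once treatment ends, "participants will continue in the follow-up phase, without treatment, until completing 52 weeks in the study". Pharmacovigilance says that "the actions to be taken by the principal investigator and sponsor in the event of an adverse event are included in Multimedia Appendix 1"; that appendix is not among the documents at hand.

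**The concern.** Stopping a drug and leaving a trial are different events. The pregnancy rule shows that the authors know the difference, but they apply it there only. A site that follows the adverse-event sentence to the letter would end follow-up for a patient who merely cannot take more tablets.

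The outcome at stake is the main one: "The sustained abstinence rate will be determined in each of the three treatment arms at 6 and 12 months", based on CO readings that are taken at in-person visits. A reading that was never taken cannot be recovered by any later analysis plan. The patient also drops out of the 1-year safety comparison promised under Specific Outcomes (Safety). These exits are caused by treatment, and planned exposure differs by arm (25, 50 or 75 days), so balance across arms is not assured.

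**Working it through.** **1. What the texts say side by side.** The adverse-event and investigator rules remove the patient from the study; the pregnancy rule keeps the patient in. Ethical Considerations repeats removal from the study, outside any heading about treatment. The Trial Design sentence on follow-up to week 52 applies after the end of treatment and does not override a mandatory withdrawal rule. It does show that follow-up off drug is already part of the design.

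**2. What a withdrawn patient misses.** Table 3 schedules CO readings at visits 1, 2, 4, 8, 9, 10, 11, 13 and 14, which is 9. Those after day 75 (visit 7) are visits 8, 9, 10, 11, 13 and 14, which is 6. Drug ends by day 75 in every arm, so a patient withdrawn while on drug misses all 6. Adverse-event checks appear in Table 3 at visits 2, 3, 5, 6 and 7, that is, up to day 75. Textbox 2 agrees (days 7, 15, 25, 50 and 75) and lists ECG, liver, electrolyte and renal checks at days 25, 50 and 75. Whatever of these is still due is lost as well.

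**3. The plan's own numbers.** Sample Size Determination gives 110 per arm and 21% loss: 110 × 1.21 = 133.1, rounded up to 134 per arm, and 3 × 134 = 402. The loss allowance is 402 − 330 = 72 patients.

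**4. How many might leave.** The document gives no rate for this trial. The only figure is 2.9% stopping cytisinicline for an adverse event, in the placebo-controlled trial of 6 and 12 weeks described in the Background. Assumption: 2.9% leave in Arm C, so 0.029 × 134 = 3.89. The split across arms is unknown, so three are shown. Maximum tablets from the dosing schedule are 101, 151 and 201 in arms A, B and C; days are 25, 50 and 75.

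| Split | A | B | C | Total | CO readings lost (×6) | Share of 72 |
|---|---|---|---|---|---|---|
| Equal | 3.89 | 3.89 | 3.89 | 11.7 | 69.9 | 16.2% |
| By tablets | 1.95 | 2.92 | 3.89 | 8.8 | 52.5 | 12.2% |
| By days | 1.30 | 2.59 | 3.89 | 7.8 | 46.6 | 10.8% |

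**5. Effect on the C minus A contrast.** Assume true abstinence of 40% in every arm, so that any difference is spurious. Let f be the fraction leaving an arm.

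- Leavers are all smokers and are excluded: the observed rate is 40/(1 − f). By days, C is 40/(1 − 0.029) = 41.20 and A is 40/(1 − 0.00967) = 40.39, a difference of +0.80. By tablets +0.60; equal 0.
- Leavers are 40% abstinent but are counted as smokers: the observed rate is 40 × (1 − f). By days, 38.84 − 39.61 = −0.77. By tablets −0.58; equal 0.

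**6. Range.** Half and double the rate are assumptions too. At 1.45%, 3.9 to 5.8 patients leave and the difference is at most 0.39 points either way. At 5.8%, 15.5 to 23.3 patients leave and the difference lies between −1.55 and +1.67. The planned difference between C and A is 50 − 30 = 20 points.

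**The case against.** The strongest reply is that this is loose wording in a condensed article. The section heading, the qualifier on the adverse-event rule, the noncompliance sentence and the last paragraph all concern treatment, and Multimedia Appendix 1 may well keep these patients in follow-up. Ethical Considerations speaks only of a possibility of withdrawal. This is fair, and it limits confidence that data would in fact be lost. It does not remove the need for a correction: an appendix that kept patients in follow-up would contradict the words in two sections of the protocol.

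Four stronger readings are tempting, and the documents do not support them.

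- **That every serious adverse event ends participation.** The rule covers only events that prevent continuation.
- **That long-term safety monitoring is the main loss.** Scheduled adverse-event checks stop at day 75, so keeping patients to week 52 adds none after that. Table 3 as shown also has no ECG or laboratory row, and its visits at days 25, 50 and 75 are by telephone. The gap between this schedule and the promised 1-year comparison is a separate matter.
- **That longer treatment must produce more exits.** The Background hypothesises no excess of adverse events with longer use, and the Discussion reports none from earlier trials. On that footing the exits are equal and the spurious difference is zero.
- **That the 2.9% predicts study withdrawal here.** It counts drug discontinuation. Sixteen patients at 2.9% implies about 550, so it pools both active durations of that trial, which the Discussion describes as using 3 mg every 8 hours, against 1.5 mg every 12 hours in the extensions here. It sets only an order of magnitude.

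**Conclusion.** The point holds and is minor. Taken literally, the protocol removes from follow-up patients whose adverse event prevents continuation, allows the same for an investigator's safety concern, and in Ethical Considerations adds failure to comply. That last ground sits awkwardly beside the rule that noncompliance does not stop treatment. Each patient withdrawn on drug loses 6 of 9 CO readings for a reason related to treatment.

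A reader might infer that the efficacy comparison is in danger; it is not. With 2.9% leaving in Arm C, 40% true abstinence in all arms and exits in Arm A between one third of and equal to those in Arm C, the bias is 0 to 0.8 points in either direction. Doubling the rate brings it to at most 1.7 points, against a planned 20. The case for change is that the loss is avoidable and cannot be repaired afterwards, not that it is large. Whether it would occur depends in part on Multimedia Appendix 1, which is not shown.

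**What to change.** In the discontinuation criteria, in Ethical Considerations and in the patient information, state that:

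- an adverse event or an investigator's safety concern stops the study drug only;
- noncompliance does not end follow-up;
- the patient then completes the remaining Table 3 visits to week 52, and any checks still due to day 75, as is already provided for pregnancy;
- only withdrawn consent ends follow-up.

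Bring Multimedia Appendix 1 into line. The criteria for stopping the drug stay as they are.

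The cost is a wording amendment with matching patient information, and visits that are already planned for a handful of patients (about 8 to 12 at the assumed rate). The Results section describes 12 preselected patients who had not yet had their first visit, so an early correction protects the most data.

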### Treatment Adherence Strategies

Adherence to treatment will be determined by checking blister packs at each visit and patient declaration.

### Prohibited, Permitted, and Rescue Concomitant Medication

The following are prohibited during the research period (from the signing of informed consent until the end of the follow-up period): antituberculosis drugs, systemic hormonal contraceptives, nicotine-containing products, such as nicotine replacement therapy, and drugs metabolized by the CYP1A2 (cytochrome *P* 450 family 1, subfamily A, polypeptide 2) and CYP1A1 (cytochrome *P* 450 family 1, subfamily A, polypeptide 2) enzymes, especially those with a narrow therapeutic index (eg, theophylline, tacrine, clozapine, and ropinirole). All concomitant medications not previously mentioned are permitted. Rescue medication is not required during the study.

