### Eligibility Criteria

Male and female smokers over the age of 18 years who have smoked more than 10 cigarettes per day during the past year and during the month before the screening visit are eligible to participate in the study. Smokers must also be prepared and motivated to quit smoking (score of 7 or higher on the visual analog scale of motivation). Smokers who have received pharmacological treatment for nicotine dependence (nicotine replacement therapy, varenicline, bupropion, or cytisinicline) within the previous 3 months are excluded from participating in the clinical trial.

In addition, exclusion criteria (Textbox 1) have been designed, taking into account the considerations of the drug label. All patients meeting all inclusion criteria and no exclusion criteria are consecutively invited to participate until the calculated sample size is obtained in each center.

Exclusion criteria for the study.Renal and/or hepatic insufficiency.Over 65 years of age (due to limited clinical experience).Hypersensitivity to the active substance or to any of the excipients.Unstable angina.Recent personal history of acute myocardial infarction or recent stroke (less than 8 weeks).Clinically relevant arrhythmias or uncontrolled hypertension.History of psychiatric illness with and without treatment (panic disorder, psychosis, bipolar disorder, and depression) within the last 12 months.History of alcohol or other drug abuse within the last 12 months.Use of tobacco products other than cigarettes, e-cigarettes, or marijuana in the past month and did not agree to abstain from using these products during study participation.Patients being treated with antituberculosis drugs.Patients being treated with drugs metabolized by CYP1A1 (cytochrome *P* 450 family 1, subfamily A, polypeptide 1) and CYP1A2 (cytochrome *P* 450 family 1, subfamily A, polypeptide 2), especially those with a narrow therapeutic margin (eg, theophylline, tacrine, clozapine, and ropinirole).Pregnant or breastfeeding smokers.Women on systemic hormonal contraceptives.

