### Posttest Care Provisions

Once the study is completed, as this is a low-intervention trial, posttrial care is not required that differs from standard clinical practice. In this case, if the participant quits smoking, he/she will be discharged from the SCU; if not, he/she will remain a patient in the SCU, and an alternative smoking cessation treatment (change of intervention format or combination of drugs) will be considered.

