Other qualities of the smoker, such as the degree of motivation and self-efficacy, will be evaluated by the Analogue Visual Scale. This scale numerically identifies a smoker’s level of motivation and self-efficacy to quit smoking. A score above 7 indicates high motivation and self-efficacy to quit smoking [27].

The EQ-5D scale will be used in this clinical trial to assess the quality of life of smokers and its changes during the smoking cessation process. This scale measures the health status of smokers using 5 dimensions, including mobility, self-care, activities of daily living, pain and discomfort, and anxiety and depression. Participants score from 0 to 100 in each domain [31].

The urge to smoke in this study will be analyzed using the Craving Rate Score. This scale assesses anxiety or intense desire to smoke at baseline and during follow-up. It is scored from 0 to 4 [32].

The additional tests that will be performed on smokers participating in this trial include electrocardiogram, carbon monoxide levels, complete blood count, and a biochemical profile that includes liver enzymes, electrolytes, and renal function tests. Co-oximetry allows for the objective identification of smoking status, as well as confirmation of abstinence at each participant visit. A participant is identified as a nonsmoker when their CO levels measured by co-oximetry are below 10 ppm (Textbox 2).

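### Varenicline and bupropion bar entry but are permitted on study by default, the text conflicts on non-study cytisinicline, and the stated abstinence criteria ignore such use

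*Protocol article*

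**What the plan says.** - **Entry (Eligibility Criteria).** "Smokers who have received pharmacological treatment for nicotine dependence (nicotine replacement therapy, varenicline, bupropion, or cytisinicline) within the previous 3 months are excluded". Four treatments are named.
- **On study (Prohibited, Permitted, and Rescue Concomitant Medication).** The section applies "from the signing of informed consent until the end of the follow-up period". Its list contains antituberculosis drugs, systemic hormonal contraceptives, "nicotine-containing products, such as nicotine replacement therapy", and drugs metabolized by CYP1A1 or CYP1A2. It then states "All concomitant medications not previously mentioned are permitted" and "Rescue medication is not required during the study".
- **Assigned course (Trial Design, Intervention).** Arm A receives the data-sheet regimen of 25 days. Once the assigned course ends, every arm is followed off treatment to week 52.
- **After the study (Posttest Care Provisions).** For those still smoking once the study is complete, "an alternative smoking cessation treatment (change of intervention format or combination of drugs) will be considered".
- **Outcome (Data Collection Variables, Limitations, Efficacy Analysis).** "A participant is identified as a nonsmoker when their CO levels measured by co-oximetry are below 10 ppm". The Limitations section adds patient self-report. The dichotomous efficacy variable is to come from an algorithm written after all study data have been obtained.

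**The concern.** The arms are meant to differ only in how long cytisinicline is taken. Any other cessation drug taken before the 6- or 12-month assessment changes what the comparison measures. The protocol treats four drug groups as important enough to bar entry, yet carries only one of them into the on-study prohibition, and its default sentence lets in whatever is not listed. That is an express rule in the section a site would consult, so it is more than detail left to a fuller document.

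Several features make the gap matter here. The trial is open-label and run in cessation units, with a marketed drug funded by the national health system (Introduction). The rationale says that 25 days leaves some smokers with uncontrolled craving and that 20% resume smoking in the two months after treatment. Control patients therefore have a reason to seek more treatment. By the Discussion's own account, one further pack of 100 tablets at 2 a day lasts 100 / 2 = 50 days, which is Arm C's extension.

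If control patients who are still abstinent take additional drug, Arm A is credited with its effect and the contrast shrinks.

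**Working it through.** **Step 1. The four drug groups side by side.**

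| Drug group | Use in the 3 months before entry | Consent to week 52, concomitant-medication section | Other text |
|---|---|---|---|
| Nicotine replacement | excluded | prohibited | consistent |
| Varenicline | excluded | not listed, so permitted by default | alternative cessation treatment mentioned only after the study |
| Bupropion | excluded | not listed, so permitted by default | same |
| Non-study cytisinicline | excluded | not listed, so permitted by default | conflicts with the assigned course and untreated follow-up in Trial Design |

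The documents do not say whether any of the last three belongs to the CYP1A1/CYP1A2 class, and I have not assumed that it does.

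**Step 2. How the outcome would treat a user.** CO and self-report concern smoking; neither takes account of other cessation drugs. On those criteria alone, a user who does not smoke is classed as a nonsmoker. No section says that such use counts as failure, is censored or is ignored.

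**Step 3. The plan's own sample size.** Inputs from Sample Size Determination: rates of 30%, 45% (the bracket beside it gives .40) and 50%; alpha 0.05; power 80%; 110 per arm; 21% loss.

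- Global three-group chi-square test (2 df). Mean rate = (0.30 + 0.45 + 0.50)/3 = 0.4167. Effect = (0.01361 + 0.00111 + 0.00694)/(0.4167 × 0.5833) = 0.0891. The noncentrality needed for 80% power is about 9.635, so n = 9.635/0.0891 = 108.1 per arm. Power at 110 is 80.7%, so the stated 110 is reproduced closely.
- Total: 110 × 1.21 = 133.1, rounded up to 134; 3 × 134 = 402, as stated.

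**Step 4. Assumed dilution of Arm A versus Arm C.** Let f be the share of all Arm A patients who reach the 75-day rate. The documents give no f. Then pA = 0.30 + 0.20f and pC = 0.50. For a two-sided 5% test with n = 110 per arm:

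Power = Φ{[(pC − pA) − 1.96·√(2p̄(1 − p̄)/n)] / √([pA(1 − pA) + pC(1 − pC)]/n)}, where p̄ = (pA + pC)/2.

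At f = 0: (0.20 − 1.96 × 0.06606)/0.06467 = 1.09, giving 86.2%.

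| f (assumed) | Arm A rate | C − A | Power, A vs C | Power, global test (45% in Arm B) |
|---|---|---|---|---|
| 0 | 30% | 20 points | 86.2% | 80.7% |
| 5% | 31% | 19 points | 82.3% | 75.9% |
| 10% | 32% | 18 points | 77.9% | 70.5% |
| 20% | 34% | 16 points | 67.4% | 58.5% |

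The pairwise test and its two-sidedness are my assumptions; the plan states neither.

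**The case against.** **Trial Design contradicts a free permission.** A reader might infer that a control patient may properly take the longer regimen and breach nothing. The documents do not support that. Arm A is assigned 25 days and follow-up is described as off treatment, so extending cytisinicline departs from allocation. This stands, and it makes the cytisinicline issue a conflict between sections. It does not settle the matter: the phrase may mean study treatment only, and it applies only after the assigned course, so it does not address varenicline or bupropion during it.

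**The permission might be narrower.** The default sentence could be read against the whole article, including the drugs named under eligibility. That is possible but strained; it most naturally refers to the list immediately before it.

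**Counting as abstinent is not settled.** A reader might also infer that a user will be scored as a success. The CO rule identifies a nonsmoker at a visit, and the efficacy algorithm does not yet exist. The documents are silent on the point.

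**Most failures cannot be rescued.** The planning outcome is sustained abstinence. On its ordinary meaning, a patient who has relapsed and then takes another drug has already failed. Arm A's assumed 70% failure rate is therefore no measure of the exposure. Only patients still abstinent when they start the drug can dilute this endpoint, although point abstinence is more exposed. This stands.

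**The size is hypothetical and the bias conservative.** Step 4 assumes full benefit and no such use in Arms B or C. Dilution in a superiority trial costs power and does not create a false claim for longer treatment. This also stands, and it limits the severity.

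**Handling is a choice.** Analysing as randomised whatever else was taken is legitimate and suits a trial framed around routine practice. Counting users as failures is not the only defensible rule.

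**Conclusion.** The inconsistency is real. Read as written, varenicline and bupropion bar entry when recently used but are permitted from consent to week 52. On non-study cytisinicline, the Trial Design and concomitant-medication sections conflict. The stated abstinence criteria do not account for use of any of the three, and the algorithm that could do so is deferred until all data are in, in an open-label trial.

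The likely direction is dilution, through control patients who are still abstinent when they take the extra drug. Its size cannot be derived from the documents. Under the assumed scenario, 5%, 10% or 20% of Arm A reaching the 50% rate would take A-versus-C power at 110 per arm from 86% to 82%, 78% or 67%. These figures show sensitivity to an assumption and should not be read as an expected loss.

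Detection could be weak where it matters. Adherence relies on blister checks at visits and patient declaration, but in Table 3 the visits at days 25, 50 and 75 are by telephone, with no in-person visit between day 21 and day 90. Severity: should fix.

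**What to change.** 1. Reconcile Trial Design, Eligibility Criteria, the concomitant-medication section and Posttest Care Provisions so that nicotine replacement, varenicline, bupropion and non-study cytisinicline are treated consistently through week 52. Which use is clinically acceptable is for the sponsor to decide.
2. Record any non-study cessation drug, with start and stop dates, at the visits already scheduled, including the telephone visits, alongside the abstinence statement. Unrecorded use is hard to recover later, so this should start early; the Results section reports only 12 preselected patients.
3. Before outcome data are seen, state how such use enters the abstinence outcome. Either handling (user counted as not abstinent, or use ignored) can be primary if stated in advance; run the other as a sensitivity analysis.

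Cost: a wording amendment, one added question and one added analysis. Counting users as not abstinent may lower the abstinence rates slightly.
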